## Abstract

**Introduction:**

Breastfeeding is associated with improved maternal and child outcomes. Women with a higher body mass index (BMI), who comprise about 50% of the population, are at increased risk of poorer breastfeeding practices and are a population who would benefit from breastfeeding.

**Methods:**

This protocol is for a multi-centre, randomised controlled trial of perinatal breastfeeding support among primiparous women with a BMI >25 kg/m^2^, using a previously-tested, multi-component intervention. The primary outcome is any breastfeeding at 3 months. The intervention will support mothers and their partners and spans from late pregnancy to six weeks postpartum. Intervention components include group antenatal breastfeeding education, individual face-to-face education in the immediate postnatal period, professional support to six weeks’ postpartum and weekly phone calls in the immediate postpartum period from an International Board Certified Lactation Consultant (IBCLC). The intervention will target attitudes towards breastfeeding, breastfeeding self-efficacy, and subjective norms around infant feeding with the aim to normalise the behaviour.

**Results:**

We anticipate that the intervention will be well-accepted and feasible to carry out within four maternity units in the East of Ireland. Furthermore, essential formative qualitative work has been conducted to inform the intervention design and to ensure that it is contextually appropriate.

**Conclusion:**

The proposed intervention will be invaluable to policy-makers in providing insights into what specific interventions are effective in improving breastfeeding rates for women with a raised BMI.

## Introduction

1

Breastfeeding provides optimal nutrition for infants and children from birth to two years and beyond [1]. For a woman, the benefits include supporting her in returning to her pre-pregnancy body mass index (BMI), better pregnancy spacing, and a lower risk of breast cancer and diabetes later in life [2]. The infant benefits include lower long-term risk of developing obesity and type 2 diabetes [2]. Wider community benefits of increased breastfeeding are gained through increased parent presenteeism at work and longer term better health in the woman [2]. Irish breastfeeding rates are amongst the lowest worldwide [2,3] with only 60% of Irish newborns receiving any breastmilk and of that percentage, 50% are exclusively breastfed on discharge from the maternity services [4]. Other developed countries such as Australia, have 96% breastfeeding on discharge and exclusivity rates of 62% at four months [5]. Health promotion strategies are in place to support increased breastfeeding and the Irish National Breastfeeding Action plan documents the need for a 2% year-on-year increase in any breastfeeding if any progress is to occur [6].

Women with overweight or obesity are an identified population sub-group that have low breastfeeding success [7]. While breastfeeding initiation rates in women with a raised BMI are 13% lower than women with a healthy BMI [7], the drop off is steep once breastfeeding has started. Women with overweight or obesity are 76% and 83% less likely to be BF at 6 weeks and 6 months, respectively, compared to women with a healthy BMI [8]. Successful multifaceted breastfeeding support intervention elements include: health professional-led education, non-health professional-led counselling and peer support interventions [9]. Interventions embedded into standard care; ongoing scheduled postpartum visits; tailored interventions to population needs; interventions delivered by health professional or peers or a mix of both; and face-to-face support improved longer term breastfeeding outcomes [10]. A recent pilot of a multidimensional breastfeeding intervention was successfully carried out among 100 women, representing all weight classifications, at The National Maternity Hospital, Dublin and Wexford General Hospital, Wexford [11,12]. Primiparous women received an antenatal group education class, a one-to-one International Board Certified Lactation Consultant (IBCLC) consultation after birth and access to online resources, follow-up phone calls from an IBCLC, and a breastfeeding support group. The intervention found exclusive breastfeeding at 3 months was increased compared to national prevalence, well-accepted and feasible to carry out in both urban and rural areas [11]. The pilot identified that mothers with a BMI >25 kg/m^2^ were less likely to exclusively breastfeed at 3 months [12] and were a potentially important sub-group to target within a fully powered randomised trial.

This study aims to investigate the effectiveness of a multicomponent breastfeeding support intervention on the prevalence of any breastfeeding at 3 months among women with a BMI >25 kg/m^2^. It is hypothesised that women in the intervention group will have higher prevalence of breastfeeding initiation, longer breastfeeding duration and higher breastfeeding self-efficacy than those in the control group. It is also anticipated that the inclusion of the support partner will improve the support-structure for women in their home setting.

## Methods

2

### Trial design

2.1

Latch On is a multicentre randomised clinical trial to test the effectiveness of an education and support intervention program, for women with overweight or obesity, during pregnancy and the first six weeks postnatal on increasing breastfeeding prevalence at three months postpartum. The flow of participants through the study from recruitment to completion is illustrated in Fig. 1. Ethical approval was granted by National Maternity Hospital Ethics Committee in December 2018 (ref: EC.24.2018). The trial was prospectively registered (ISRCTN14819650), initial planning started on August 1^st^, 2018 and recruitment commenced on June 4^th^, 2019. Recruitment from March 12^th^, 2020 to date (April 2021) has been impacted by the covid-19 pandemic.

**Fig. 1 fig1:**
[figure not shown]
**Flow chart for The Latch On Study;** *recruitment and intervention impacted by covid-19 pandemic: March 12^th^, 2020 until present (April 2020, and likely this will be the case until recruitment is completed); face-to-face recruitment did not continue during this period, face-to-face antenatal classes were also suspended during this time with online classes offered as an alternative. Drop-in clinics were available by appointment only.

### Recruitment and eligibility

2.2

#### Recruitment

2.2.1

Recruitment began on June 4^th^, 2019 and the anticipated end date is November 2022. The recruitment sites are: National Maternity Hospital, Dublin (NMH); Wexford General Hospital, Wexford (WGH); St Luke's General Hospital, Kilkenny (SLK); and Midlands Regional Hospital, Mullingar (MRH). The project is part funded by the HSE Nursing and Midwifery Planning and Development Unit Dublin South, Kildare and Wicklow and sponsored by 10.13039/501100001631University College Dublin (UCD).

The NMH, based in the city centre of Dublin, Ireland's capital, is one of the largest maternity hospitals in Europe with approx. 9000 births per year. WGH is a smaller regional hospital in Wexford, Ireland, with approximately 2000 babies delivered each year. Similarly, SLK and MRH are regional hospitals with approximately 1600 and 1900 births each year respectively.

Recruitment strategies vary due to site-level differences in staffing, care delivery and timing of routine visits and include recruitment within antenatal clinics, with researchers or midwives approaching women in early pregnancy to the beginning of the third trimester. Posters are displayed throughout hospital maternity units and on hospital websites. Social media, including Twitter and Instagram are also used as a recruitment channel. At all sites, lists of the reasons for refusal to take part in the study are documented to keep a record of why participants did not wish to take part. Women were also free to decline participating without providing an explanation.

The COVID-19 pandemic emerged during the study and recruitment was adapted. Participants recruited between June 4^th^, 2019 and March 12^th^, 2020 were enrolled prior to covid-19 (n = 105); all participants recruited after 12th March 2020 were enrolled during the covid-19 pandemic. Staff were limited in the time they could allocate to assist with the study during the pandemic, and therefore recruitment was mainly via self-referral from in-house notices and hospital websites, with pregnant women interested in the study contacting the research team about participating. Recruitment strategies were adapted with face-to-face recruitment in antenatal clinics reduced. At the NMH, the study was publicised in antenatal clinics via posters, through social media such as Twitter and Instagram, and also promoted at online antenatal classes. The charts of women attending antenatal clinics are now screened by researchers for eligibility, and those deemed eligible subsequently contacted via phone and provided with verbal information on the study. If they are interested in taking part, further information and consent forms are sent to them via email. At the regional hospital sites, the study was also publicised via posters, through social media, and promoted at online antenatal classes. Recruitment phone calls were also adapted at these sites where possible.

Face-to-face antenatal classes were moved to online virtual classes with follow-up phone calls offered as an alternative. Postnatal 1-1 consults were possible with IBCLC's at each hospital site. Postnatal breastfeeding drop-in clinics were also cancelled, and these clinics were instead offered by appointment only.

An outline of the PICO (population, intervention, comparison, outcomes) for the Latch On Study is included in Table 1.

**Table 1 tbl1:** PICO (population, intervention, comparison, outcomes) for the Latch On Study.

Population	Inclusion criteria • Primiparous women • Singleton pregnancy • BMI ≥25 kg/m^2^ at booking visit • Age ≥18 years • Good understanding of English • Ability to give informed consent • Have a support partner available and willing to participate if in intervention group Exclusion criteria • Preterm (<37 weeks' gestation) delivery • Any condition requiring medication that is contraindicated for breastfeeding
Intervention	Intervention components include: • Group antenatal education for prospective mothers and their support partners • Individual education for new mothers in the immediate postnatal period^a^ • Professional support for new mothers to six weeks postpartum
Comparison	Control group will receive: • Routine antenatal care • Oral and written information on antenatal and postnatal breastfeeding support available in the study site hospital and community
Outcome	Primary outcome: • Breastfeeding at 3 months postpartum Secondary outcomes: • Intention to breastfeed following the antenatal component of the intervention • Initiation rates of breastfeeding • Exclusive and any breastfeeding prevalence at hospital discharge, 6 weeks, 3 months, and 6 months postpartum • Maternal and support partner attitudes toward breastfeeding • Breastfeeding self-efficacy • A comparison of breastfeeding prevalence, duration, self-efficacy and support structures among women who delivered pre-pandemic and during the pandemic

a Immediate postnatal period: women were usually seen by an IBCLC anytime during their hospital stay.

#### Assessment of eligibility

2.2.2

Depending on the setting, electronic health records or traditional paper charts are used to screen women for eligibility in advance of women attending their antenatal appointment. Information on general sociodemographics, gestational age, reproductive history and pre- and early gestational weight gain will be obtained through interview with the participant.

#### Inclusion criteria

2.2.3

Women are eligible if they are aged 18 or older, are identified as having a BMI of 25 kg/m^2^ or higher at their first antenatal visit; primipara; singleton pregnancy; 26–34 weeks pregnant at recruitment; proficient in English; able to give informed consent; have an identifiable support partner available, and are willing to participate in the trial. Support partners could be the baby's father, the pregnant woman's male or female partner, the pregnant woman's mother or sister or a trusted friend.

#### Exclusion criteria

2.2.4

Preterm delivery (<37 weeks’ gestation) and any known/identified breastfeeding contraindications, inclusive of any conditions requiring medication contraindicated for breastfeeding.

#### Informed consent

2.2.5

When women are approached, either in person or via phone calls, the study protocol is explained to them and they are asked if they are interested in taking part. Participating women are asked to provide signed informed consent within the same clinic visit if possible when recruitment is in person. If they would like more time to consider the study, they are given time to review study information and a consent form to complete and return to researchers. Researchers schedule a follow-up phone call for 2–3 days after this.

#### Randomisation

2.2.6

Women are allocated to either intervention or control using a computer-generated scheme. Randomisation is a 1:1 allocation and stratified by study site and BMI category (CSTAR, UCD). Given the nature of the intervention, neither the participants nor the researchers are blinded to allocation. Sealed opaque envelopes will be sequentially numbered and treatment will be allocated automatically through selection of the next available envelope. Researchers select a sealed envelope in numerical order, open the envelope and will then advise the woman of the group they have been allocated to. Women receive a phone call after they have provided consent to take part in the study.

#### Control

2.2.7

Women assigned to the control group are provided with oral and written information on antenatal and postnatal support for breastfeeding that is available in the study site hospital and community, and will receive routine antenatal care. A summary of the information available to women in the control group is available in Appendix A.

#### Intervention

2.2.8

This multi-component intervention targets prospective mothers and their support partners and spans the perinatal period from late pregnancy to six weeks’ postpartum. Intervention components include group antenatal education for prospective mothers and their support partners, individual education for new mothers in the immediate postnatal period, and professional support for new mothers to six weeks postpartum (Table 2). Women allocated to the intervention group attend a group antenatal education session usually between 28–36 weeks gestation with their support partner.

**Table 2 tbl2:** Intervention approaches used.

Approach	Description	Timing
SMS texts	Welcome to the study text with links to online questionnaires. These texts are standardised to ensure all participants received the same text. SMS texts are sent to participants in both the intervention and control groups.	Post randomisation
Email	Welcome to the study email with links to online questionnaires. Also used to send links to late pregnancy and postnatal questionnaires (6 weeks, 3 months and 6 months postpartum). These emails are standardised with all participants receiving the same email. Emails are sent to participants in both the intervention and control groups.	Throughout the study
Phone call from researcher	Researchers will phone participants to randomise them to a study group, and also to schedule the antenatal class and to give reminders about completing the online questionnaires. Phone calls from researcher to participants occur for both the intervention and control groups.	Throughout the study
Group education	Antenatal class – the antenatal class covers a range of topics in relation to breastfeeding rates, the benefits of breastfeeding, the basics of breastfeeding, and breastfeeding support. The antenatal classes are delivered by lactation consultants. Pregnant women and their support partners are required to attend the antenatal class. Intervention group only.	28–36 weeks
Individual consultation	IBCLC will provide face to face advice and support after the birth of the infant. Intervention group only.	1–3 days postpartum
Phone call from IBCLC	IBCLC will phone mother weekly to discuss her progress and issues she is having. Self-efficacy prompts. Intervention group only.	Once per week for 6 weeks postpartum
Breastfeeding support group clinic	IBCLC led drop-in weekly clinic made available to mothers for the first 6 weeks postpartum. Intervention group only. Breastfeeding support clinic is by appointment only during the covid-19 pandemic.	Once per week for 6 weeks postpartum

During the covid-19 pandemic (from 12th March 2020 onwards), changes to the provision of the intervention components were made. All antenatal classes now take place virtually, and postnatal drop-in clinics are now taking place by appointment only. Women receive postnatal follow-up support over the phone from lactation consultants for the first 6 weeks postpartum, with an in-person appointment arranged if needed or requested.

The intervention has been mapped onto the COM-B behaviour change framework with a focus on attitudes to breastfeeding, changing subjective norms and perceived behavioural control (Appendix B). Attitudes toward breastfeeding are targeted by providing education in the antenatal and postnatal period to mothers and their support partners. Subjective norms around infant feeding are targeted by providing education to the pregnant woman's support partner, and by facilitating breastfeeding support groups postpartum which will be attended by other breastfeeding mothers, normalising the behaviour. The mother's perceived behavioural control of her ability to feed her baby (breastfeeding self-efficacy) is targeted by providing antenatal and postnatal education that is realistic and describes what to expect when breastfeeding, including potential challenges that may arise and how to manage these challenges. This education equips women with the skills and confidence to manage breastfeeding, increasing their self-efficacy.

#### Antenatal class

2.2.9

Pregnant women and their support partners are asked to attend an antenatal class at 28–36 weeks gestation. This class covers a range of topics in relation to breastfeeding rates, the benefits of breastfeeding, the basics of breastfeeding, and breastfeeding support. The antenatal classes are delivered by lactation consultants. Attendance at the antenatal class is compulsory for the support partner and they will be provided with specific information on how they can support the breastfeeding mother. All support partners were encouraged to attend the class; however, if a support partner was unable to attend, this was recorded and they were provided with information to read through in their own time, or a second antenatal class was arranged for a time the partner could attend. A copy of the antenatal class checklist is included in Appendix C, which outlines the content covered at the class.

#### Individual face-to-face education

2.2.10

After the birth of the infant, an IBCLC provides the participant with face-to-face advice and support. The IBCLC covers aspects such as breast assessment, infant oral assessment, what to expect in the first few days, how to attach and recognise the baby is effectively feeding, as well as other elements such as ensuring a minimum of 8 feeds per 24 h, and knowing how to hand express. Details of newborn feeding method are collected at this face-to-face session and a breastfeeding assessment is completed by the IBCLC. Any other issues or challenges are also assessed at this session. Finally, a LATCH assessment is completed by the IBCLC. The postnatal assessment checklist (Appendix D) gives details of what is covered at this education session. The preference is for an in-person consultation with an IBCLC. If a mother is discharged prior to a lactation review they receive a telephone consult as soon as possible after discharge. Video calls are also arranged if required. A note of how 1-2-1 consultations were delivered to participants is recorded.

### Professional support up to six weeks postpartum

2.3

#### Drop-in clinics

2.3.1

Before the covid-19 pandemic, drop-in clinics were offered in a group setting to all participants allocated to the intervention group at their maternity unit. The age of the baby, relevant medical and breastfeeding history and information on any breastfeeding challenges were discussed at this drop-in clinic. Self-efficacy and a latch assessment are also completed and notes of a plan and follow-up are recorded where relevant. Drop-in clinics are by appointment only during the covid-19 pandemic, or a video call arranged if they cannot attend in person. A drop-in clinic checklist can be found in Appendix E.

#### Weekly phone calls

2.3.2

Education is reinforced by weekly phone calls in the postpartum period from an IBCLC to answer any questions. The IBCLC discusses the woman's progress and any issues she may be having. The lactation consultant records details in relation to breastfeeding history, and also notes any breastfeeding challenges that were discussed with the participant. Self-efficacy of the mother is also prompted, and notes for a plan and follow-up recorded where relevant. A follow-up phone call checklist is included in Appendix F.

### Data collection

2.4

#### Process and impact evaluation

2.4.1

Midwives and IBCLC are provided with individual logins for the Latch-On online platform. This allows them to schedule antenatal classes and drop-in clinics in conjunction with the researchers at the primary study site (UCD/NMH). Process checklists to be completed by IBCLC include the antenatal class checklist, and the drop-in clinic checklist. Pregnancy outcome and pregnancy complications will be collected from hospital charts as per our usual pregnancy studies.

### Outcome measures

2.5

#### Primary outcome

2.5.1

The primary outcome is feeding method at 3 months' postpartum, assessed using self-reported questionnaires completed by the mother, including the Questionnaire on Infant Feeding by O'Sullivan et al. [13].

#### Secondary outcomes

2.5.2

The secondary outcomes include:1.Intention to breastfeed following the antenatal component of the intervention, assessed by open ended and closed ended questions in a questionnaire completed by the mother at pre-antenatal class2.Initiation rates of breastfeeding, collected using hospital discharge data at discharge from hospital3.Exclusive and any breastfeeding prevalence assessed using a questionnaire completed by the mother (including Questionnaire on Infant Feeding (O'Sullivan et al., 2017) [13]), at hospital discharge, 6 weeks', 3 months' and 6 months' postpartum.4.Maternal and support partner attitudes toward breastfeeding, assessed by open ended and closed ended questions in a questionnaire completed by the mother at pre-antenatal class, 6 weeks', 3 months', and 6 months' postpartum.5.Breastfeeding self-efficacy, assessed using Breastfeeding Self-Efficacy Short Form (Dennis, 2003) [14], at pre-antenatal class, 6 weeks', 3 months', and 6 months' postpartum6.Additional outcome related to COVID-19 pandemic: A comparison of breastfeeding prevalence, duration, self-efficacy and support structures among women who delivered pre-pandemic (June 2019–Feb 2020) and during the pandemic (March 2020-TBC).

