#### Baseline and follow-up measurements [outcome]

2.6.1

Women and their partners complete the below antenatal questionnaires at baseline and late pregnancy. Where possible, validated questionnaires are used. If a validated questionnaire was not available, a self-designed questionnaire was used. The women's questionnaires include measurement of:•Breastfeeding (Attitude to breastfeeding)•Feeding Confidence•Infant Feeding Attitude•Breastfeeding Attrition Prediction Tool (BAPT) Survey•Breastfeeding Support

The support partner completes the below antenatal questionnaires at baseline and late pregnancy:•Breastfeeding (Attitude to breastfeeding)•Breastfeeding Support

Women and their partners are sent an email with a link to their questionnaires, and the researchers make a follow-up call if required to remind them to complete these.

Mothers complete a range of questionnaires at 6 weeks, 3 months, and 6 months postpartum to collect information on Feeding Details, Feeding Decision, Breastfeeding Experiences, Feeding Confidence, Infant Feeding Attitude, Breastfeeding Support, Cost Diary, Quality of Life, and Postnatal Depression.

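### Secondary outcome 1 is defined as intention to breastfeed after the antenatal component, but its only stated assessment comes before the antenatal class

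*Protocol article*

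**What the plan says.** Section 2.5.2 (Secondary outcomes) gives the first outcome as "Intention to breastfeed following the antenatal component of the intervention, assessed by open ended and closed ended questions in a questionnaire completed"; the same sentence, read to its end, says it is "assessed by open ended and closed ended questions in a questionnaire completed by the mother at pre-antenatal class". It gives no later assessment. Table 1 repeats the definition without a time.

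Table 1 describes the antenatal part of the intervention as "Group antenatal education for prospective mothers and their support partners". Section 2.2.9 dates it: "Pregnant women and their support partners are asked to attend an antenatal class at 28–36 weeks gestation". Table 2 marks this class as given to the intervention group only.

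Section 2.6.1 describes two antenatal waves: "Women and their partners complete the below antenatal questionnaires at baseline and late pregnancy". Table 2 adds that links to the late-pregnancy and postnatal questionnaires are emailed to both arms. Neither place lists intention among the measures, and neither says whether the late-pregnancy wave comes before or after the class.

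**The concern.** The definition and the time point cannot both hold. A value collected before the class is a pre-exposure value with respect to the class.

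An analyst who took the stated time would compare the arms before the class had been delivered. A null result could then be reported as the class having no influence on intention, although the data could not have shown one. A non-null result could be credited to the class when it could only reflect chance or a reaction to knowing one's allocation. Either conclusion would be unsupported.

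The outcome matters for interpretation. Section 2.2.8 says the intervention works partly by changing attitudes and confidence through antenatal education. Intention measured after the class and before birth is the listed outcome that could show what the antenatal part does on its own, before postnatal support begins.

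**Working it through.** The protocol gives no figure for this outcome, so the check is of sequence rather than arithmetic.

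1. **What counts as the antenatal component.** Table 1 lists three components: group antenatal education, individual education just after birth, and professional support up to six weeks postpartum. In Table 2 the individual consultation falls at 1–3 days postpartum, and the weekly calls and clinics run for 6 weeks postpartum. The texts, emails and researcher calls go to both arms. The class is therefore the only antenatal element that differs between arms.

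2. **Order of events in the intervention arm.** The definition in 2.5.2 requires class, then measurement. The stated time requires measurement, then class. These are opposite orders within one sentence.

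3. **Control arm.** Table 2 restricts the class to the intervention group, so a time expressed relative to the class has no anchor among controls.

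4. **Comparison with a neighbouring item.** Self-efficacy (outcome 5) is assessed "at pre-antenatal class, 6 weeks', 3 months', and 6 months' postpartum". There the pre-class value starts a series that has three later points. Outcome 1 has the pre-class point and nothing after it.

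5. **Whether another section supplies the missing time.** Section 2.6.1 and Table 2 establish that a late-pregnancy questionnaire exists in both arms. They do not tie it to intention or place it after the class. Because the class may fall anywhere from 28 to 36 weeks, an undated late-pregnancy wave could come on either side of it.

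6. **Whether a post-class, pre-birth time is feasible.** Delivery before 37 weeks is an exclusion. From the class to the earliest delivery among eligible women there are 37 − 28 = 9 weeks for the earliest class and 37 − 36 = 1 week, or slightly less, for the latest. A window exists but is short for late classes.

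7. **Whether the pre-class score is a clean baseline.** Section 2.2.6 says neither participants nor researchers are blinded. Table 2 dates the welcome text, with its questionnaire links, after randomisation. The early questionnaire may therefore be answered by women who already know their arm.

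8. **Reach of the problem.** The sample size in section 2.8 concerns the primary outcome only. Its figures reproduce with the uncorrected two-proportion formula: 40% versus 60% gives 97 per arm (194 in total, power 0.8003), and 50% versus 70% gives 93 per arm (186 in total, power 0.8000). Neither depends on outcome 1.

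**The case against.** The strongest reply is that this is a slip in one phrase. A later antenatal wave exists, it goes to both arms, it sits under a heading about follow-up measurement, and it may well be the intended assessment. An article condenses a fuller protocol, and analysis of secondary outcomes is commonly left to an analysis plan that is not shown. The sentence also contradicts itself, so nobody can strictly follow it, and how a result would be reported is a prediction.

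Much of this stands. It limits the seriousness of the point and makes the late-pregnancy wave the natural remedy. It does not remove the contradiction: the time is not omitted but stated, and it conflicts with the definition. An analysis plan can choose among data collected, but it cannot move a measurement to after the class.

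A reader might infer several stronger things that the document does not support:

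- *That outcomes 4 and 5 share the error.* Neither is defined as following the antenatal component, and both have assessments at 6 weeks, 3 months and 6 months. Their schedules are coherent.
- *That the late-pregnancy data will go unused.* Nothing says so.
- *That the power for a class effect is exactly the 5% type I error.* No test or significance level is given for this outcome. If women answer after learning their allocation, the arms may differ for that reason, and the rejection rate need not be 5%.

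**Conclusion.** The time point stated for secondary outcome 1 is wrong for the outcome as defined. At that time a between-arm comparison carries no information about the effect of the class, at any sample size. This rests on the class being the only antenatal component that differs between arms, as Tables 1 and 2 show, and on the time in 2.5.2 meaning what it says.

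The size is modest: one of six listed secondary outcomes, with no consequence for the primary outcome, its analysis or the sample size. A reader might take it as a threat to the trial's main conclusion; the document gives no ground for that. If the late-pregnancy questionnaire was always the intended assessment, follows the class and contains the intention item, correcting the wording is enough. The article does not establish any of these three conditions.

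**What to change.** In 2.5.2, set the assessment of outcome 1 at the late-pregnancy questionnaire described in 2.6.1 and Table 2. State that it is completed after the class in the intervention arm, at a comparable gestation in controls, and before delivery in both. Confirm that the existing intention item is in that questionnaire, and add it if not.

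Use the earlier intention score as a baseline covariate only where it was completed before the woman was told her allocation. Otherwise report it descriptively, because adjusting for a score that knowledge of allocation may have altered can bias the comparison.

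The cost is a change of wording, timing the late-pregnancy email to follow the class, and possibly one existing item. Women already past that point cannot be measured in retrospect, so the number with a valid post-class value should be reported by arm. A late-pregnancy time point for outcomes 4 and 5 is optional.
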